### Statistical analysis

2.9

Statistical analyses will be conducted using SPSS version 22 (IBM Corp., Armonk, NY, USA). Data will be expressed as mean number ± standard deviation and frequency (percentage), as appropriate. Clinical scores and radiologic properties of the IVD at different time points during follow-up will be assessed using the paired *t*-test or Wilcoxon signed rank test, according to the normality of the population, which will be determined using D'Agostino-Pearson omnibus tests [13]. A two-tailed probability level of 0.05 will be considered significant. Continuous data will be analysed using linear mixed models, as such models are robust in longitudinal data analysis and account for correlations associated with repeated measurements [12]. As recommended by the revised Consolidated Standards of Reporting Trials statement, the mixed models will adjust for the baseline score of the outcome of interest [12,29]. Original data will be analysed using the Mann-Whitney *U* test. The risk ratio, risk difference, and number needed to treat will be calculated, together with 95% confidence intervals [12,29,30]. Statistical significance will be determined by χ^2^ analysis.

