## Abstract

Herniated nucleus pulposus (NP), one of the most common diseases of the spine, is surgically treated by removing the sequestered NP. However, intervertebral disc (IVD) defects may remain after discectomy, leading to inadequate tissue healing and predisposing patients to IVD degeneration. An acellular, bioresorbable, ultra-purified alginate (UPAL) gel (dMD-001) implantation system can be used to fill any IVD defects in order to prevent IVD degeneration after discectomy. This first-in-human pilot study aims to determine the feasibility, safety, and perceived patient response to a combined treatment involving discectomy and UPAL gel implantation for herniated NP. We designed a one-arm, double-centre, open-label, pilot trial. The study started in November 2018 and will run until a sample of 40 suitable participants is established. Patients aged 20–49 years, diagnosed with isolated lumbar IVD herniation and scheduled for discectomy represent suitable candidates. All eligible participants who provide informed consent undergo standard discectomy followed by UPAL gel implantation. The primary outcomes of the trial will be the feasibility and safety of the procedure. Secondary outcomes will include self-assessed clinical scores and magnetic resonance imaging-based measures of morphological and compositional quality of the IVD tissue. Initial outcomes will be published at 24 weeks. Analysis of feasibility and safety will be performed using descriptive statistics. Both intention-to-treat and per-protocol analyses of treatment trends of effectiveness will be conducted.

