### Sample size

2.7

This is a first-in-human pilot study designed to generate data that can be used to inform a future large randomised controlled trial should the intervention appear feasible and safe, and show trends of effectiveness. To date, no data has been published on the quantitative interactions of a biomaterial with the IVD tissue and how such interactions might affect the IVD space after discectomy. Therefore, we could not conduct a priori sample size calculations for this pilot study because the effect size cannot be estimated at this time. The study aims to recruit 40 participants [12] because we expect that such a sample size will be achieved within a reasonable time based on the study recruitment rates within our community. Moreover, a sample size of 40 participants is considered sufficient for an exploratory clinical trial because it allows to detect with 95% probability differences in one or more adverse events that exhibit an incidence ratio of 7.5%. We aim to evaluate key trial parameters such as preliminary indications of effectiveness and to advise of our calculation of a sample size for powering a full trial in the future [27]. Published guidelines recommend that pilot studies be undertaken to allow trial protocols to be tested under study conditions prior to evaluation in a full randomised controlled trial [12,28]. Thus, the results of this limited phase II trial will also assist in determining the relevance and possible benefits of performing a significantly larger phase III randomised controlled trial [12].

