### Feasibility and safety analysis

2.8

Data regarding feasibility and safety will be analysed using descriptive statistics [27]. The percentage of participants who (i) meet the inclusion criteria, (ii) agree to participate in this study, (iii) complete the intervention, and (iv) attend the follow-up assessment will be calculated. Feasibility will be described in terms of the (i) number of follow-up sessions attended by each participant, (ii) number of drop-outs, and (iii) proportion of participants recruited from the total number screened [27]. Additionally, feasibility will be evaluated as the rate of completion of UPAL gel implantation, which will be judged according to the adequacy of gelation of the surface of the injected UPAL solution after application of CaCl_2_ solution. The rate of completion of UPAL gel implantation will be assessed as the number of patients with adequate gelation divided by the number of patients who undergo discectomy followed by UPAL solution injection. Safety will be assessed as the rate of adverse events and reactions.

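### Section 2.9 ends with two-group statistics (risk ratio, risk difference, NNT, Mann-Whitney U, chi-square) that have no second group in a one-arm trial

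*Protocol article*

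**What the plan says.** The Abstract fixes the design: "We designed a one-arm, double-centre, open-label, pilot trial", and "All eligible participants who provide informed consent undergo standard discectomy followed by UPAL gel implantation". Under Discectomy (2.5.1), a patient who meets a stopping criterion before implantation gets no gel and leaves the trial, so these patients form no comparison group.

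Statistical analysis (2.9) begins with methods that suit one arm. Clinical scores and radiologic properties over time go to the paired t-test or the Wilcoxon signed-rank test, and continuous data go to linear mixed models adjusted for baseline.

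Its last three sentences change character:

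- "Original data will be analysed using the Mann-Whitney" U test. What counts as original data, and which two groups are compared, is not stated.
- "The risk ratio, risk difference, and number needed to treat will be calculated, together with 95% confidence intervals". No event and no comparator are given.
- "Statistical significance will be determined by" chi-square analysis. The table to be tested is not given.

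For the primary outcomes, section 2.8 says: "Data regarding feasibility and safety will be analysed using descriptive statistics". The only control group mentioned anywhere is in the Discussion: an observational discectomy-only historical control study, to be done once this trial is finished. Section 2.9 does not refer to it.

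**The concern.** These three sentences are positive commitments that the design cannot meet. They are not details left for a fuller document. An analyst following the section must either drop prespecified analyses or invent a contrast after seeing the data.

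The comparator closest to hand is each patient's own pre-operative state. Every patient has a discectomy as well as the gel, so a before-and-after NNT would mix the two effects and present the sum as if it belonged to the gel. Section 2.7 says that the pilot should show trends of effectiveness and inform a later randomised trial, so such a figure could mislead the decision that the pilot is meant to support.

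For the two tests, the stake is ambiguity. If they are applied to visits of the same patients, section 2.9 prescribes both a paired and an unpaired rank test for the same data, and the two can disagree.

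**Working it through.** **1. The plan's own figure.** Section 2.7 justifies the target of 40 on the ground that "it allows to detect with 95% probability differences in one or more adverse events", taking an incidence of 7.5%. The word differences might suggest two groups. As a one-sample statement:

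- P(at least one event) = 1 − (1 − 0.075)^40 = 1 − 0.925^40 = 0.956, which reproduces the stated 95%.
- As a two-group comparison of 7.5% with 0% (two-sided 0.05), power would be 23% with 20 per group and 42% with 40 per group. That does not reproduce it.

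The sample-size statement is therefore a one-arm calculation and needs no comparator.

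**2. Risk ratio, risk difference and NNT.** With p1 the event risk on treatment and p0 the risk in a comparison group:

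- RR = p1 / p0; RD = p1 − p0; NNT = 1 / |RD|.
- The trial yields p1 only. With p0 undefined, none of the three has a value.

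Suppose the pre-operative state is used as p0. The change in each patient is then the discectomy effect, plus any gel effect, plus natural course and regression to the mean, and one arm cannot separate them. Leg pain shows this plainly. Section 2.3 requires a leg-pain VAS score above 40 at entry. If response means a score of 40 or less, p0 = 0 by the entry rule, so RD equals the follow-up response rate q and NNT = 1/q, whether or not the gel does anything.

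**3. Mann-Whitney U and chi-square on paired visits.** This is an illustration only, because section 2.9 does not say that they will be used this way.

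From the document: 40 patients, two-sided 0.05. Assumed, because the document gives no values: normal data, pre-post correlation 0.3, 0.5 or 0.7, and a 0.4 SD shift for power. For the binary tests, the same data were cut at a fixed threshold, the baseline mean. There were 10,000 simulated trials per setting.

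| Quantity | Correlation 0.3 | 0.5 | 0.7 |
|---|---|---|---|
| Type I error, Mann-Whitney | 2.0% | 0.7% | 0.1% |
| Type I error, signed-rank | 5.0% | 5.0% | 5.0% |
| Type I error, chi-square | 3.4% | 2.1% | 0.9% |
| Type I error, McNemar | 4.9% | 4.7% | 4.3% |
| Power, Mann-Whitney | 39% | 36% | 36% |
| Power, signed-rank | 53% | 67% | 88% |
| Power, chi-square | 28% | 26% | 24% |
| Power, McNemar | 34% | 38% | 47% |

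With an assumed 0.5 SD shift and correlation 0.5, Mann-Whitney power is about 60% against about 86% for the signed-rank test (86 to 87% in separate runs). The type I error at that correlation was 0.7 to 0.8% across runs. The direction is expected: positive correlation reduces the variance of the within-patient difference, and an unpaired test does not use this.

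**4. What one arm can report.** The exact (Clopper-Pearson) upper 95% limit for 0/40 is 1 − 0.025^(1/40) = 8.8%. By the same method 1/40 gives 0.1 to 13.2%, and 39/40 gives 86.8 to 99.9%.

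**The case against.** The strongest defence is that a second group could exist. There are two centres, section 2.5.1 treats extrusion- and sequestration-type herniations separately, and the historical control study is to use the same evaluation protocol. Mann-Whitney and chi-square could be computed on such groups. This stands in part: for those two tests the supported defect is that the groups are not named, not that computation is impossible. It does not rescue the NNT, because a contrast between centres or hernia types is not a treatment effect, and the control study is separate, later and not mentioned in section 2.9.

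A reader might also infer more than the document supports:

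- **That the binary outcomes have no valid analysis.** They do. Section 2.8 defines descriptive rates, including the implantation completion rate with its numerator and denominator, and section 2.9 provides for frequencies and percentages.
- **That the absence of an interval on the primary rates is itself an error.** An interval method for a descriptive rate may sit in the full protocol or the SAP, neither of which is shown.
- **That Pfirrmann grade will be tested wrongly.** It is a radiologic property, which section 2.9 already sends to the paired tests. The Mann-Whitney sentence speaks of original data, not ordinal data.
- **That the chi-square sentence contradicts the descriptive primary analysis.** It does not mention feasibility or safety, so a contradiction with section 2.8 is possible but not shown.
- **That false positives would rise.** Under positive correlation the unpaired tests are conservative, and the cost is power. The pilot states no power target for these outcomes.

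Brevity of a journal article explains omissions. It does not explain a stated commitment that the design cannot meet.

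**Conclusion.** The point holds for the last three sentences of section 2.9, which are wrong as written and should be fixed. The risk ratio, risk difference and NNT are undefined within this trial; that follows from the single arm and needs no assumption. Mann-Whitney U and chi-square lack named groups. The loss shown above arises only if they are applied to two visits of the same patients, and its size rests on the assumed correlations, shifts and normal data.

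The descriptive primary feasibility and safety analysis, the rationale for 40 participants, the paired tests and the mixed models all stand. The trial's main conclusions do not depend on the faulty sentences, so this is not a critical defect. The main risk is a misleading NNT.

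**What to change.** - Delete the risk ratio, risk difference, NNT, Mann-Whitney U test and chi-square test from this trial's analysis. Alternatively, move them to the plan of the later discectomy-only historical control study, with the comparator and the event defined there.
- Within this trial, keep the signed-rank test for ordinal change and use McNemar's test for paired binary change.
- In place of the two-group intervals, report single-arm proportions with exact (Clopper-Pearson) two-sided 95% intervals.

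The cost is a wording change in section 2.9. No patients, visits, data or sample size are affected.

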## Discussion

3

The main aim of this study is to examine the feasibility and safety of the combined treatment involving discectomy and UPAL gel implantation for herniated NP. In addition, measures of physical function scores, self-reported questionnaires for evaluating pain and health-related quality of life and MRI analysis for evaluating the IVD are performed to investigate perceived patient response to the procedure as secondary outcome measurement. Although surgeon can decide whether alginate implantation is feasible, resulting in a possible selection bias, the reason for stopping the implantation will be recorded and the feasibility will be analysed. This is a first-in-human pilot study designed to generate data that can be used to inform a future, large, randomised controlled trial should the intervention appear feasible and safe, and show trends of effectiveness. After the completion of this clinical trial, an observational study will be conducted as a historical control study in patients with lumbar disc herniation who have undergone discectomy only, using the same evaluation protocol as in this clinical trial.

## Trial registration

The protocol of this study has been registered with the University hospital Medical Information Network Clinical Trials Registry (UMIN-CTR) (trial registration number: UMIN000034227. Registered 21 September 2018).
